### Randomization and blinding

After the baseline visit, participants are randomized with a 1:1 ratio to either the intervention group or control group. Block randomization (in variable groups of two and four) stratified for study centre and diagnosis (SCD or MCI) is used. Randomization is done by a computer-generated allocation scheme integrated in the Castor electronic data capturing system (Castor EDC, Amsterdam, The Netherlands). Researchers executing cognitive assessments at follow-up are blinded for group allocation. Group allocation is not actively disclosed to participants, but complete blinding is unlikely due to the nature of the intervention.

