### Sample size

For power calculation, we used mean scores of the primary outcome, the LIBRA2 score, in people with SCD and MCI as reported in a previous study [31]. A 1-point difference in LIBRA2 scores between the intervention and control group at the end of the study would translate into a Cohen’s d = 0.35. To detect such a small to moderate effect size with 80% power in two-sided testing at an alpha-level of 0.05 and a 1:1 treatment allocation ratio, 133 patients per group are needed. Further assuming a 10% dropout rate during the trial means that we need 148 participants per group, resulting in a total sample size of 296, which was rounded up to 300.

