#### Effectiveness analysis

We will use linear mixed model analyses to test the effect of the intervention on the primary and secondary outcome variables (except secondary measures collected for process evaluation and cost-effectiveness) as these models generally handle missing outcome data well and thereby align with the intention-to-treat principle, even if only baseline values are available [63]. Models will use a random intercept (individuals) and, if likelihood ratio testing suggests better fit, random slopes (time). Treatment group (intervention or control) and time (baseline and 1-year follow-up) will be included as fixed effects, and study site and diagnostic group (SCD or MCI) as fixed covariates. Additional covariates will be added if randomization was not successful in balancing other characteristics (e.g. age, gender and education) between treatment groups. An interaction term between treatment group and time will be included as fixed effect. The intention-to-treat principle is used by including all randomized participants in the analyses, including dropouts and non-adherent participants. Missing primary and secondary outcome data are considered as missing-at-random (i.e., missingness is probabilistic and conditional on the covariates included in the analyses) and handled efficiently through maximum likelihood estimation of expected scores in the linear mixed model [64]. We will additionally assess differences in effectiveness and adherence between the SCD and MCI groups using stratified analysis. All analyses will be two-sided at an alpha level of 0.05 and conducted in Stata 18 or higher. A per-protocol sensitivity analysis will be performed to assess whether results remain consistent when excluding participants with low adherence to the intervention.

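### The plan sets out to assess whether the effect differs between SCD and MCI but names only stratified analysis, and nothing in it tests that difference

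*Protocol article*

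**What the plan says.** The Effectiveness analysis section of the protocol article gives both an aim and a method for the two diagnostic groups: "We will additionally assess differences in effectiveness and adherence between the SCD and MCI groups using stratified analysis".

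The same section describes the main mixed model. Diagnosis has a main-effect role only, with "study site and diagnostic group (SCD or MCI) as fixed covariates". One interaction is named: "An interaction term between treatment group and time will be included as fixed effect". The significance rule is general: "All analyses will be two-sided at an alpha level of 0.05".

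Diagnosis is also a randomisation factor. Under Randomization and blinding, block randomisation "stratified for study centre and diagnosis (SCD or MCI) is used". The article gives neither an expected SCD:MCI split nor a quota for either group, and the Sample size section addresses the overall comparison only.

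**The concern.** Whether the effect differs between SCD and MCI is a question about one quantity: the effect in SCD minus the effect in MCI. In its ordinary sense, a stratified analysis fits the model separately in each group and gives two effects with two p-values. It neither estimates that difference with a confidence interval nor tests it. Nothing else in the article does so.

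Each stratum holds only part of a sample sized for the whole trial, so power within a stratum is moderate at best. When power is near one half, two strata with the same true effect will often fall on opposite sides of 0.05. A reader shown one significant and one non-significant stratum could conclude that the intervention works in one diagnostic group only, when the data do not show that.

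**Working it through.** **Inputs from the Sample size section.** The effect is a 1-point LIBRA2 difference that "would translate into a Cohen’s d = 0.35", which implies an SD of 1/0.35 = 2.86 points. The size is set "with 80% power in two-sided testing at an alpha-level of 0.05 and a 1:1 treatment allocation ratio, 133 patients per group are needed". For dropout: "Further assuming a 10% dropout rate during the trial means that we need 148 participants per group".

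**The plan's own figure.** The normal approximation is n = 2(1.960 + 0.842)² / 0.35², which rounds up to 129 per group. The t-test version gives 129.1, so 130. The stated 133 is slightly higher and therefore conservative; power at 133 is 81.4%. The dropout step is exact: 133/0.9 = 147.8, so 148 per group and 296 in total.

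**Assumptions.** 133 are analysed per arm. The true effect is the same in SCD and MCI. The SCD:MCI split is not in the document, so 50:50 to 30:70 is used. Calculations are in SD units at follow-up, as in the plan's own sample size.

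**Formulas.** With n per arm in a stratum, SE = √(2/n) and power ≈ Φ(d/SE − 1.96). With powers p₁ and p₂, the chance that exactly one stratum is significant is p₁(1 − p₂) + p₂(1 − p₁). The SE of the difference in effect is √(2/n₁ + 2/n₂). For a smaller-stratum share f, its ratio to the overall SE is 1/√(f(1 − f)).

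**Results at a common d = 0.35.**

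| Split | n per arm in each stratum | Power in each stratum | Exactly one significant | SE ratio |
|---|---|---|---|---|
| 50:50 | 66.5 / 66.5 | 52% / 52% | 50% | 2.00 |
| 40:60 | 53.2 / 79.8 | 44% / 60% | 51% | 2.04 |
| 30:70 | 39.9 / 93.1 | 35% / 67% | 55% | 2.18 |

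Worked case at 50:50: SE = √(2/66.5) = 0.173; 0.35/0.173 − 1.96 ≈ 0.06; power 0.523; 2 × 0.523 × 0.477 = 0.50. At 30:70: 0.346 × 0.334 + 0.666 × 0.654 = 0.55. Using the t distribution lowers the stratum powers by about one percentage point and leaves the last two columns essentially unchanged. With 135 per arm (300 less 10%), the chances are again 50%, 51% and 55%.

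**Other common effects, over the same splits.** At d = 0.2 exactly one stratum is significant in about 33-34% of trials, and at d = 0.5 in about 29-41%. With no effect in either group it is 2 × 0.05 × 0.95 = 9.5%. The value 0.5 stands in roughly for the precision that baseline scores may add in the mixed model; the article gives no baseline correlation from which to compute it.

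**Comparison with an interaction test.** Its false-positive rate is 5% in all these settings, confirmed by simulation at 135 per arm. At d = 0.35, an interaction test would also be significant in only 8-10% of the trials with one significant stratum.

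**Power of the interaction test.** The SE of the difference is √(4/66.5) = 0.245 at 50:50 and √(2/39.9 + 2/93.1) = 0.268 at 30:70. For a true difference in effect of 0.35 SD (1 point), power is Φ(0.35/0.245 − 1.96) ≈ 30% and Φ(0.35/0.268 − 1.96) ≈ 26%. The difference detectable with 80% power is 2.80 × SE, about 0.69 SD (2.0 points) and 0.75 SD (2.1 points).

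**The case against.** The strongest objection is that the article does not prescribe comparing p-values. A stratified analysis can be reported as two estimates with confidence intervals. The difference of two independent stratum estimates divided by its standard error is a valid test, close to the interaction term. The sentence is also one line on an additional analysis in a condensed article, and the details could sit in an analysis plan that is not shown.

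Part of this stands. The rates above apply only if the strata are read by their separate significance, which the general 5% rule permits but does not require. The objection does not remove the point. The article states an aim and chooses a tool for it, and that tool alone does not answer the aim. This is a stated choice and not merely a detail left out.

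A second objection is that the interaction has low power and the primary result does not depend on it. Both statements are true. They argue for an exploratory label and a confidence interval, and they give no support to separate stratum p-values.

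Two stronger readings are tempting and are not supported.
- A reader might infer that a false contrast would steer implementation to the wrong group. No section makes implementation depend on the SCD/MCI contrast. The Conclusions look to all memory clinic patients who might benefit, the Discussion ties roll-out to (cost-)effectiveness, and the heterogeneity named under Cost-effectiveness analysis is demographic and socio-economic.
- A reader might extend the criticism to adherence, which the same sentence covers. SCD and MCI can be compared directly on adherence within the intervention arm, so no error is shown there.

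**Conclusion.** The point holds for effectiveness. The plan aims to assess a difference in effect between SCD and MCI and specifies nothing that tests it. If the strata are judged by their separate results, a common true effect gives a false contrast in about half of trials at the design effect, roughly three to four in ten at a common d of 0.2 or 0.5, and about one in ten with no effect, against one in twenty for an interaction test. These figures rest on 133 analysed per arm, an assumed split of 50:50 to 30:70, and a comparison at follow-up that ignores any gain from baseline scores.

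The primary estimate, its error rate and the sample size are untouched. What is at risk is interpretation: a report could suggest benefit in one diagnostic group only. The change should be made, but it concerns an additional analysis and does not threaten the trial's main conclusion.

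**What to change.** For the SCD/MCI question, fit the full-sample mixed model with a treatment by time by diagnosis interaction and its lower-order terms. Report the interaction estimate, which is the difference in one-year effect between the groups, with its 95% CI. Derive the effects in SCD and in MCI from that same model and present them as descriptive. State that the analysis is exploratory because its power is low, and that significance in one group alone will not be taken as evidence of a difference.

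The cost is one additional model and one or two sentences. Diagnosis is already recorded and already a randomisation stratum, so no new data, participants or change to randomisation are needed, and the primary analysis stays as written.

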### Control group

The control group receives general health advice through a similar binder, including the same general information about the LIBRA2 factors in relation to brain health and dementia. Participants in both groups will receive regular online newsletters and updates as well as gift vouchers (75 euros in total) for their participation.

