### Primary outcome

The primary outcome is the 1-year change in participants’ modifiable dementia risk profile as measured by the LIBRA2 score (Fig. 2). LIBRA2 comprises of 15 modifiable dementia risk and protective factors identified through an umbrella review and expert consensus study: coronary heart disease, diabetes, hypercholesterolemia, hypertension, depression, obesity, smoking, high physical activity, chronic kidney disease, high alcohol intake, high cognitive activity, healthy diet, hearing impairment, sleep disturbances, and social participation [4, 22]. Each of these factors has an assigned weight based on the factor’s relative risk for dementia from meta-analyses as shown in Supplementary Table 1 [23]. Based on the presence or absence of risk or protective factors, these weights are summed to yield a total LIBRA2 score. Higher scores indicate an unhealthier lifestyle profile and a higher risk of dementia, with a total score ranging from − 6.1 to 25.7. LIBRA2 was constructed in 2024 and represents an update of the original LIBRA index, in which three risk- and protective factors were added (hearing impairment, sleep, social participation). The LIBRA index has been extensively validated to predict brain damage, cognitive decline, incident cognitive impairment and dementia in various population-based studies [28–30] and clinical studies in people with SCD or MCI [31, 32]. LIBRA2 is recently validated in the English Longitudinal Study of Ageing and the Maastricht Ageing Study, showing increased overall performance compared to LIBRA [23]. Yet, validation in clinical samples remains to be established. It has also been included as outcome measures in other multidomain intervention studies targeting the general population [14, 16, 33, 34] and the ongoing 2-year multidomain FINGER-NL trial [35], and has been recommended as a surrogate outcome measure in prevention studies by the World Health Organization’s brain health group [36] and the World Wide FINGER group [20]. Table 2 describes the measurement of each LIBRA2 factor in this study, including the cut-offs that will be applied to assess the presence of the risk factors.

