#### Adherence

Additionally, adherence measures will be recorded to track real-world feasibility and implementation. Adherence measures include the number of appointments with the lifestyle coach or research visits missed, the number of personal goals set and reached, the number of vouchers provided and their usage, and a usage log of BreinZorg (login times, completion of learning modules).

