## Discussion

This design paper provides an overview of the rationale and study design of LIGHT, a 12-month multicenter RCT investigating the effects of a personalized multidomain lifestyle intervention to improve brain health in memory clinic patients. This study will show if a lifestyle intervention including three counselling sessions with a lifestyle coach, a voucher program and an online self-management platform is (cost-)effective and possible to implement in Dutch hospitals.

Translating intentions into actual and sustainable health behavior on the long-term is challenging and involves many individual barriers, such as socio-economic status and access to (affordable) resources, social support, and health literacy [68, 69]. To increase involvement in the intervention, participants will be individually guided by a coach across three sessions [70]. The use of motivational interviewing helps participants to articulate their own desires and their underlying reasons. This has been shown to be effective in the motivation to change behaviors and increase adherence to lifestyle intervention programs [71]. By implementing a personalized intervention, in which participants formulate their own targets and goals to fit their individual needs together with a coach, we aim to increase internal motivation of participants to successfully change their behavior and maintain this newly adopted behavior in the long term.

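### The per-protocol check drops low adherers to an intervention that only one arm receives, so it cannot be relied on to show that the intention-to-treat result holds

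*Protocol article*

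**What the plan says.** The main analysis in the protocol article (Effectiveness analysis) is by intention to treat: "The intention-to-treat principle is used by including all randomized participants in the analyses, including dropouts and non-adherent participants." The effect of interest is the group-by-time interaction in a linear mixed model. The same section then adds: "A per-protocol sensitivity analysis will be performed to assess whether results remain consistent when excluding participants with low adherence to the intervention."

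The Adherence section lists what is recorded: "Adherence measures include the number of appointments with the lifestyle coach or research visits missed, the number of personal goals set and reached", then "the number of vouchers provided and their usage, and a usage log of BreinZorg". Under Personalized lifestyle intervention, the coach sessions, the goals set with the coach, the vouchers and BreinZorg are all components of the intervention. For the other arm, the Control group section says: "The control group receives general health advice through a similar binder." Both arms receive gift vouchers for taking part, but these are separate from the voucher programme.

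The endpoint is a change score: "The primary outcome is the 1-year change in participants’ modifiable dementia risk profile as measured by the LIBRA2 score" (Primary outcome).

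**The concern.** Low adherence to the intervention can be scored only in people who were offered it. A control has no coach appointments to miss and no programme vouchers to leave unused. Whatever cut-off is chosen, the exclusion falls on one arm.

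The selection is unlikely to be neutral. Much of LIBRA2 scores lifestyle behaviour: diet, physical and cognitive activity, smoking, alcohol and social participation. People who keep coaching appointments may be those who would have improved anyway. The article itself ties motivation to adherence when it says of motivational interviewing: "This has been shown to be effective in the motivation to change behaviors and increase adherence to lifestyle intervention programs" (Discussion).

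At stake is how the check is read. The article gives it the job of showing whether results remain consistent. A similar or larger per-protocol effect would pass as reassurance, and in a trial meant to inform implementation it could be taken to mean that the programme works when used. Selection alone could produce that pattern.

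**Working it through.** **The plan's own figure.** Sample size gives d = 0.35 for a 1-point difference, so the implied SD is 1/0.35 = 2.86 points. A two-sample t-test at d = 0.35, two-sided 0.05 and 80% power needs 130 per group; an unrounded d of 0.345 gives the stated 133. Then 133/0.90 = 147.8, so 148 per group and 296 in total. The sample size is sound, and 133 per arm is used below.

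**Inputs.**
- From the article: SD 2.86; 133 evaluable per arm; analysis of change.
- Assumed, because the article gives no value: equal SD at both visits; baseline-to-follow-up correlation r = 0.5 (0.7 as an alternative); share of the intervention arm excluded, p = 10% to 40%; correlation ρ between adherence and spontaneous improvement, 0.1 to 0.4. There is no true effect.

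**Formulas.**
- SD of change = 2.86 × √(2(1 − r)). At r = 0.5 this is 2.86; at r = 0.7 it is 2.86 × 0.775 = 2.21.
- With z the standard normal p-quantile, the retained participants have mean adherence m = φ(z)/(1 − p) in SD units.
- False benefit = ρ × m × SD of change.
- SE = √[SD² × (1 − ρ²m(m − z))/(133(1 − p)) + SD²/133], with SD that of change.
- False-benefit rate = Φ(false benefit/SE − 1.96). It is 0.025 when there is no bias.

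**Worked case, p = 20%, ρ = 0.3, r = 0.5.** m = 0.280/0.80 = 0.350. False benefit = 0.3 × 0.350 × 2.86 = 0.30 points. SE = 0.368. Rate = Φ(0.30/0.368 − 1.96) = 0.126.

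**Range at r = 0.5: points of false benefit (false-benefit rate).**

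| Excluded | ρ = 0.1 | ρ = 0.2 | ρ = 0.3 | ρ = 0.4 |
|---|---|---|---|---|
| 10% | 0.06 (0.036) | 0.11 (0.050) | 0.17 (0.068) | 0.22 (0.091) |
| 20% | 0.10 (0.045) | 0.20 (0.078) | 0.30 (0.126) | 0.40 (0.194) |
| 30% | 0.14 (0.056) | 0.28 (0.111) | 0.43 (0.200) | 0.57 (0.325) |
| 40% | 0.18 (0.066) | 0.37 (0.148) | 0.55 (0.283) | 0.74 (0.466) |

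At r = 0.7 the points shrink to about 77% of these and the rates are the same. At ρ = 0 there is no bias. At ρ = −0.2 with 20% excluded, the bias is 0.20 points against the intervention.

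**Simulation (20,000 runs per case).** For 20% excluded and ρ = 0.3, the mean false benefit was 0.30 points and the rate 0.125. For 30% and 0.3, it was 0.42 points and 0.193. Keeping everyone as randomised gave a rate of 0.025.

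**The case against.** The strongest reply is that nothing decisive rests on this analysis. It is named a sensitivity analysis, and the intention-to-treat result keeps every randomised participant. That stands, and it limits the weight of the point. It does not rescue the check, because a comparison that selection can move in either direction cannot confirm the main result.

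The second reply is that the group-by-time term protects the comparison. In part it does. If adherers are simply healthier at both visits, the difference cancels. A reader might work from the 12-month score alone: with 25% excluded and a correlation of 0.3, that gives 0.3 × 0.318/0.75 = 0.127 SD, or 0.36 points. This is not the planned estimator. Under a stable link of that kind, the bias in change is zero. Bias requires adherence to predict change.

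Other stronger readings are tempting and are not supported:
- That the analysis is certain to favour the intervention. The article gives no adherence rate and no adherence-outcome correlation, and a negative link reverses the sign.
- That adherence will be defined by goals reached. The Adherence section records "the number of personal goals set and reached, the number of vouchers provided and their usage", but the Effectiveness analysis section does not say which measures define low adherence.
- That exclusion of a control is strictly impossible. Missed research visits exist in both arms. With a single follow-up visit, however, missing it leaves no outcome, and the rule concerns adherence to the intervention.
- That the absent cut-off is itself a fault. It may be in the analysis plan, which is not shown; no cut-off would make the exclusion two-sided.

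Finally, a complier-average effect also rests on an untestable assumption. That is true, and it shapes the definition of receipt proposed below.

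**Conclusion.** The point holds in a limited form. As written, the rule produces an in-effect one-sided exclusion, so the per-protocol result should not be used to judge whether the intention-to-treat finding is consistent. The possible distortion is material against a 1-point target: about 6% of it at the mild end of the range and about three quarters at the severe end, with 30% in the middle case. These sizes rest on assumed exclusion shares and correlations, and they vanish if adherence is unrelated to change. A false benefit is the more plausible direction because the outcome largely scores lifestyle behaviour, but the documents do not establish it. The primary analysis and the sample size are not in question. The change is worth making, though the main conclusion does not depend on it.

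**What to change.** Replace the exclusion with a complier-average causal effect:
- Include all randomised participants, with randomised arm as the instrument for receipt of the intervention.
- Define receipt by coach-session attendance, fixed before unblinding, with any session attended as the main definition. A higher cut-off would treat partly coached people as untreated and so break the exclusion restriction. Vouchers are handed out at coach visits, so someone who attends none receives none.
- Adjust for baseline LIBRA2, site and diagnosis.
- Do not use goals reached to define adherence. Goals are set from the LIBRA2 profile, so this would partly select on the outcome.
- If the per-protocol table is kept, label it descriptive and drop its role as a consistency check.

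The cost is a little analysis work and no new data, since attendance is already recorded. Intervals will be wider. The exclusion restriction must be stated, and BreinZorg access without coaching may strain it.
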